## Methods / design

### Study design

The design of the INPART-study will be an unblinded, randomized controlled trial with 2 treatment conditions (experimental and control) and assessments at baseline, 3 and 6 months. It will be conducted at three study centers: the university medical centre in Leipzig, Hannover and Ulm. Following an initial screening procedure, eligible partners (necessary requirement PHQ-9 or GAD-7 > 9) will be randomized into one of two groups at which baseline-assessment will take place (see Fig. 1). Participants will be either assigned to the intervention group (IG) or to the control group (CG). T1 is 3 months after the start of the intervention. Directly after the intervention, before t1, subjects of the intervention group will have the possibility of one additional single session in order to talk about individual topics/problems (i.e. hope, death and loss). Subjects of the control group will be treated as usual (optional unspecific contacts with a psycho-oncologist). At all assessments partners and patients are asked to fill out the questionnaires. The study protocol has been approved by the ethical review boards of each of the three centres. The registered project number is DJCLS R 12/36.

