The program comprises of 5 weekly sessions lasting 1.5 h and additional home practice assignments. Groups consist of 6 to 8 participants. A presentation via Microsoft Powerpoint supports the structure of the course. In each session the participants receive material supporting the actual topic, a folder containing further information and home practice instructions for the forthcoming week. Table 2 shows the content of the INPART program per session.

**Table 2 Tab2:** Structure and content of the INPART sessions and home practice

Session	Content	Form of relaxation techniques
1	● Introduction to the course and goals of INPART	Progressive muscle relaxation (PMR)
	● Information about the specific burdens of partners of patients with cancer	
	● Identification and activation of resources	
2	● Identification of negative appraisals, interpretations and meanings ● Recognizing and down-scaling of excessive self-expectations to facilitate daily life	Guided imagery: encouragement of a benevolent companion
3	● Communication within relationship: Introduction to basic rules of successful communication, non-verbal communication, gender differences in communication	Autogenic training
4	● Dealing with emotions, (focus on anxiety)	Mindfulness-based stress reduction
	● Promotion of functional anxiety management	
	*Aim*: Reduction of dysfunctional coping and regain of control	
5	*Final session*: ● Coping in daily life	Guided Imagery: safe place
	● Outlook: taking next steps	
	● Reflection of the program	

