### Main study hypotheses

To alleviate depression as well as anxiety and to promote psychological well-being in partners of individuals with haemato-oncological disease the INPART-intervention was developed and will be tested in the proposed RCT. Principal hypothesis: A manualized group psychotherapy to treat clinically significant depressive and anxiety symptoms in partners of cancer patients with haemato-oncological disease will result in a greater reduction of depression and anxiety symptoms than in a control treatment of usual intervention (expected effect size ≥0,30) at three (t1) and six months (t2) after commencing intervention. In addition, the INPART program will lead to significant better DC. Secondary hypotheses: The INPART-intervention will result in better quality of life, better quality of the relationship and more self-efficacy than the control intervention. Between t1 and t2 a structured short-time psychotherapy in the intervention group will lead to further positive effects in the dependent variables compared to that of the treatment as usual group.

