### Assessment

#### Baseline assessment

Following initial screening data collection will take place at three different intervals: baseline (t0), 3-months follow-up (t1) and 6-months follow-up (t2). in both groups. In addition to demographic and clinical characteristics, information about the quality of the relationship, dimension of the psychological burden (fatigue, anxiety, intensity of depression), quality of life, need for support and DC skills are collected. The applied questionnaires are well established. They have been standardized and validated. Table 3 shows the assessment tools and time frames at which the questionnaires are to be presented to patients and partners.

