#### Follow-up assessments

Follow-up assessments will take place post intervention around three months after start of the intervention and at a six-month follow-up appointment. The participants will receive paper versions of the questionnaires along with return envelopes. In the case of drop-out, the researcher tries to contact the participant by phone to complete a minimum set of outcome measures and to ascertain the reasons for the drop-out.

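### Baseline is placed after unblinded randomisation, and follow-up is dated from an intervention start that is undefined for controls, so baseline-to-follow-up intervals can differ by arm

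*Protocol article*

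**What the plan says.** **Order of events.** In the protocol article, Study design puts screening first. Eligible partners then "will be randomized into one of two groups at which baseline-assessment will take place". The same section states: "The design of the INPART-study will be an unblinded, randomized controlled trial with 2 treatment conditions". The outcome scales in Table 3 are self-report questionnaires, completed by partner and patient. PHQ-9 and GAD-7 appear at screening and again at t0. BFI, SF-12, IPC, ECR-RD and DCI appear first at t0.

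**Follow-up clock.** Study design: "T1 is 3 months after the start of the intervention". Main study hypotheses sets the principal comparison "at three (t1) and six months (t2) after commencing intervention". Follow-up assessments: "Follow-up assessments will take place post intervention around three months after start of the intervention and at a six-month follow-up appointment". Baseline assessment gives both arms the same labels, "baseline (t0), 3-months follow-up (t1) and 6-months follow-up (t2). in both groups", but says nothing on what starts the clock for controls.

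**Control contact.** Study design makes contact with a psycho-oncologist optional. The Control group section describes a single structured consultation of about half an hour. Neither is dated relative to randomisation or t0, and the two descriptions need to be reconciled.

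**Group formation.** Intervention: "Groups consist of 6 to 8 participants". Randomization procedure assigns partners in balanced blocks of varying length. The article does not say that randomisation waits until a group can be formed, and it sets no limit on the time from t0 to the first session.

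**The concern.** Two features of the timing matter together.

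First, a baseline taken after allocation in an open trial is not protected by randomisation. A partner who has just learned that she will, or will not, join the programme may answer differently for that reason. The planned analysis is a repeated-measures (M)ANOVA with time as a factor, so t0 is part of the tested contrast. For dyadic coping and the secondary scales there is no earlier measurement to fall back on.

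Second, a clock that starts with the intervention is clear for one arm only. If intervention partners wait for a group while controls are followed from t0, the arms are compared at different distances from baseline. Any change in distress over time, in either direction, would then be mixed with the treatment effect. Analysis cannot fully repair this, because a missing pre-allocation DCI score and an undefined control date cannot be reconstructed.

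**Working it through.** **Inputs (Power calculation, unless stated).** N = 162; recruitment over 27 months; 3 centres; forecast participants 119, 123 and 156; 4 intervention groups per centre; group size g = 6 to 8 (Intervention); equal allocation within blocks (Randomization procedure).

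**1. The plan's own figures.**
- Forecast: 284, 292 and 372 cases per year × 27/12 = 639, 657 and 837. Multiplying by 0.75 × 0.50 × 0.50 gives 119.8, 123.2 and 156.9, which the plan truncates to 119, 123 and 156, in total 398.
- Sample size: a non-central F calculation with f = 0.25, alpha 0.05, power 0.80, numerator df 2 and six cells gives 158, or 162 after rounding up to equal cells. The point does not depend on an error in either figure.

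**2. Wait for a group to fill.** Assume even accrual, 1:1 individual randomisation, and a group that starts when full. With r intervention partners per centre per month, the first partner waits (g − 1)/r and the average wait is (g − 1)/(2r).

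| Accrual | r per month | Mean wait, months | Longest wait, months |
|---|---|---|---|
| N = 162, equal centres | 162/27/3/2 = 1.0 | 5/2 to 7/2 = 2.5 to 3.5 | 5 to 7 |
| 4 groups of 6 per centre | 24/27 = 0.89 | 5/1.78 = 2.8 | 5.6 |
| 4 groups of 8 per centre | 32/27 = 1.19 | 7/2.37 = 3.0 | 5.9 |
| Forecast, smallest centre (119) | 119/27/2 = 2.20 | 1.1 to 1.6 | 2.3 to 3.2 |
| Forecast, largest centre (156) | 156/27/2 = 2.89 | 0.9 to 1.2 | 1.7 to 2.4 |

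The mean wait is thus 2.5 to 3.5 months at the required sample size and 0.9 to 1.6 months at the forecast.

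**3. What each reading of t0 implies.** Let w be the wait.
- *t0 soon after randomisation.* Intervention partners reach t1 at 3 + w months after t0, on average about 3.9 to 6.5 months. Controls reach it at about 3 months if they are clocked from t0. The intervals differ by w, at t2 as well.
- *t0 at group start.* The intervention interval is 3 months, but t0 falls w months after allocation, and controls have no stated matching date.
- *t0 and follow-up of controls tied to group start.* The intervals agree, but t0 is still taken w months after allocation in both arms. The article does not describe this arrangement.

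None of the three removes both problems.

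**The case against.** The strongest reply is that much of this is inference. The article does not say that a group waits until it is full, that t0 is taken on the day of randomisation, that controls run on a different clock, or that allocation is disclosed before t0 is completed. The order of events rests on one loosely worded clause that refers to Fig. 1, which is not shown. Labels of baseline, 3 and 6 months in both arms fit a t0 close to group start. Controls do have a consultation that could serve as a start. Visit windows are a detail that an article may leave to the full protocol.

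This limits the point without removing it. The clause does place baseline after randomisation, and three sections date follow-up from an event defined for one arm only. The inference about waiting has some support: the pilot recruited from October to December 2017 and ran its groups in January/February 2018, although it had no randomisation. A later t0 shrinks the difference in intervals only by lengthening the gap after allocation.

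A reader might go further and infer that the design credits natural recovery to INPART, since partners enter with scores above 9 and the patient is within a year of diagnosis or relapse. One could multiply a wait of 3 months by an assumed fall of 0.05 SD per month (range 0.03 to 0.10) and obtain 0.15 SD (0.09 to 0.30), against a hypothesised effect of at least 0.30 whose metric is not named. The documents do not support this as a finding. They give no rate of change; Background describes an unpredictable illness course and no correlation between it and the partner's stress. Part of any regression to the mean after screening would also occur before t0. At forecast accrual the same assumed 0.05 gives only 0.9 × 0.05 to 1.6 × 0.05, or about 0.05 to 0.08 SD.

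For depression and anxiety, the screening scores soften the problem of a baseline taken after allocation. They do nothing for DCI or the other scales.

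**Conclusion.** The concern holds in a limited form. As written, t0 follows randomisation in an open trial with self-reported outcomes, so it can reflect knowledge of the allocation. DCI, SF-12, IPC, ECR-RD and BFI have no measurement before randomisation. Follow-up is dated from intervention start, and controls have no defined start.

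If groups start only when full and accrual is even, the mean wait is roughly a third of the nominal 3-month interval at forecast accrual, and about equal to it at N = 162. The Discussion reports participation of about 10% in the pilot, so the faster accrual should not be relied on. The intervals *can* differ by arm. The documents do not show that they will, and they establish neither the direction nor the size of a bias.

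**What to change.** 1. State that t0 is completed by partner and patient before allocation is disclosed. Where this fails, use the screening PHQ-9 and GAD-7 as the baseline covariate. They are valid for this purpose because selection above the cut-off precedes randomisation and affects both arms alike.
2. Date t1 and t2 in both arms from one common date. For example, give each control the assessment dates of the therapy group formed from the same randomisation block and centre. Dating from randomisation would also be common to both arms. With waits of up to 5 to 7 months at N = 162, however, some intervention partners would then reach t1 before their first session.
3. Record the dates of randomisation, t0, group start and each follow-up in both arms, so that the intervals can be reported.

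The cost is protocol wording, some scheduling work, and control assessment dates that depend on when a group starts. With t0 taken earlier, the interval from t0 to t1 exceeds 3 months by the wait, but comparably in both arms.

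Randomising in batches of 12 to 16 per centre is optional. At 2 partners per centre per month it takes roughly 12/2 = 6 to 16/2 = 8 months per batch. That delays entry, lets screening scores age and may lose partners.

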**Fig. 1 Fig1:**
[figure not shown]
Study procedure

### Participants and procedure

Patients and their partners are recruited at the departments of haemato-oncology at the three university medical centres (Leipzig: University Cancer Center Leipzig (UCCL), Hannover: Oncology Center (OZ), Ulm: Comprehensive Cancer Center Ulm (CCCU)) by a student assistant at each centre. Inclusion criteria requires a haemato-oncological diagnosis, being in a relationship and written informed consent for participation in the study. Partners will be contacted via the patient. Once consent from the patient has been given, partners are asked for their informed consent. Partners are randomly assigned to one of the two study groups. For participant flow see Fig. 2. For an overview of measurements and corresponding time frames see Table 3.

**Fig. 2 Fig2:**
[figure not shown]
INPART flow diagram

**Table 3 Tab3:** Measurements and corresponding time points for patient and partner

Instrument	Target	Screening		Baseline (t0)		3-month follow-up (t1)		6-month follow -up(t2)	
		Partner	Patient	Partner	Patient	Partner	Patient	Partner	Patient
Demographics		x	x						
Clinical characteristics			x		x		x		x
PHQ-9	depression	x	x	x	x	x	x	x	x
GAD-7	anxiety	x	x	x	x	x	x	x	x
BFI	Fatigue			x	x	x	x	x	x
SF-12	Quality of Life			x	x	x	x	x	x
IPC	self-efficacy			x	x	x	x	x	x
ECR-RD	Quality of Relationship			x	x	x	x	x	x
DCI	DC			x	x	x	x	x	x

Note. *PHQ-9* = Patient Health Questionnaire, *GAD-7* = Generalization Anxiety Disorder Scale, *BFI* = Brief-Fatigue-Inventory, *SF-12* = Health Survey 12, *IPC* = Internal, Powerful Others, and Chance Scale, *ECR-RD* = Experience in close Relationships-Revised, *DCI* = Dyadic Coping Inventory

### Eligibility for study participation

We include patients who are diagnosed with a confirmed haematological neoplasia: incidences up to one year after diagnose or relapse, ICD-10 diagnoses: C81-C96 and D46, which are: Hodgkin’s lymphoma, Non-Hodgkin’s lymphoma, multiple myeloma, myelodysplastic syndrome, acute or chronic leukaemia. We include patients who have a partner. Patients and partners need to be between 18 and 70 years. In order to be eligible, partners must be mentally and physically able to attend the program. Treatment modality and phase of illness is negligible for participation. Partners will be assigned to one of two study groups, given that PHQ-9 > 9 (depression) and / or GAD-7 > 9 (anxiety). Exclusion criteria for patients and partners are: a) severe psychiatric disorders, b) profound cognitive and physical impairment. An age limitation of 70 years aimed to minimise possible age-related comorbidities or mobility limitations. Exclusion and inclusion criteria will be checked in the patients’ records or in discussion with the attending physician.

### Randomization procedure

Study entry requires a positive screening result and consent from the eligible partners. During screening partners are asked to fill out the PHQ-9 (depression) and the GAD-7 (anxiety). The necessary criteria for randomization is a cut-off score > 9 in at least one of the two scales (see [21, 22]). Randomization will be carried out on a basis of fixed blocks of flexible length. Within one block the assignment is balanced meaning that the number of interventions and control subjects are the same. The different length of the blocks is chosen to further reduce predictability of the assignment.

Possible selection effects will be documented to analyse their effect on the generalization of the results. Drop-out participants will be included in an intent-to-treat-analysis. To control for potential undesired side effects, other psycho-oncological or complementary interventions are recorded and considered in the analysis as well as information from the treatment process. In the case of events during the course of the study which may influence the therapeutic implications of the intervention negatively i.e. newly occurring exclusion criteria for example cognitive impairments or mobility deterioration, participants will be excluded. Psycho-oncological or psychiatric help is ensured by the local psychosomatic consultation-liaison and the psychiatric consultation services.

### Assessment

#### Baseline assessment

Following initial screening data collection will take place at three different intervals: baseline (t0), 3-months follow-up (t1) and 6-months follow-up (t2). in both groups. In addition to demographic and clinical characteristics, information about the quality of the relationship, dimension of the psychological burden (fatigue, anxiety, intensity of depression), quality of life, need for support and DC skills are collected. The applied questionnaires are well established. They have been standardized and validated. Table 3 shows the assessment tools and time frames at which the questionnaires are to be presented to patients and partners.

#### Follow-up assessments

Follow-up assessments will take place post intervention around three months after start of the intervention and at a six-month follow-up appointment. The participants will receive paper versions of the questionnaires along with return envelopes. In the case of drop-out, the researcher tries to contact the participant by phone to complete a minimum set of outcome measures and to ascertain the reasons for the drop-out.

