#### Control group

The control group receives one structured psycho-oncological consultation (Control condition/Care as usual), which is regularly conducted by trained psycho-oncologists The duration of the consultation is approximately 30 min. Example issues discussed consist of the role of partner within the course of the illness including their own specific burdens and possibility of support. In addition they will receive a freely accessible booklet from the German Cancer Aid associated to their specific oncological disease.

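### Drop-outs' outcomes are collected by a researcher's phone call and everyone else's on paper, so mode follows drop-out status and could become related to arm

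*Protocol article*

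**What the plan says.** Under Follow-up assessments, the standard mode is self-completion at home: "The participants will receive paper versions of the questionnaires along with return envelopes". The next sentence makes a different provision for some participants: "In the case of drop-out, the researcher tries to contact the participant by phone to complete a minimum set of outcome measures". The rest of that sentence gives the call a second purpose, finding out why the person dropped out.

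Five other statements bear on this:

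- Study design: "The design of the INPART-study will be an unblinded, randomized controlled trial with 2 treatment conditions".
- Randomization procedure: drop-outs are kept in an intent-to-treat analysis.
- Measures and Power calculation: the PHQ-9 is described as a self-report tool, and PHQ-9 and GAD-7 are the outcome criteria behind the sample size.
- Baseline assessment: the time points are the same for everyone, "baseline (t0), 3-months follow-up (t1) and 6-months follow-up (t2). in both groups". The phone rule is not arm-specific either.
- Intervention and Control group: "The program comprises of 5 weekly sessions lasting 1.5 h and additional home practice assignments", whereas "The control group receives one structured psycho-oncological consultation", lasting about 30 minutes.

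**The concern.** A mood scale filled in privately and the same scale answered aloud to a member of the study team need not give the same score. Here the change of mode comes with a change of collector, and the collector also asks why the person left. In this trial that question would usually reveal the arm, because only intervention partners attend group sessions. Because drop-outs are analysed as randomised, any shift due to mode enters the main comparison of PHQ-9 and GAD-7.

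An equal shift spread equally over both arms would cancel. The risk is that it is not spread equally. If drop-out includes stopping the sessions, intervention partners have five occasions to meet the trigger and control partners have almost none. The article's own pilot points the same way: homework was felt as a burden (Intervention), and willingness to make a weekly one-hour drive was low (Discussion). Part of any arm difference could then be a difference in how the outcome was taken. If the mode is not recorded at the time, this cannot be examined later.

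**Working it through.** **The plan's own figure.** The article gives no figure for mode of collection. Its only related figure is N = 162 at f = 0.25, alpha 0.05 and power 0.80. A noncentral F calculation with 6 cells (2 groups × 3 centres), numerator df 2 and noncentrality f² × N = 0.0625 × N needs N = 158, or 162 when rounded up to equal cells (power at 162 = 0.813). The figure is reproduced in that setting and does not depend on mode. It is used here only to fix the yardstick d = 2f = 0.50 for two equal groups.

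**Inputs from the article**

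- Hypothesised effect of at least 0.30 (Main study hypotheses). Its metric is not stated; it is read here as SD units.
- f = 0.25 (Power calculation).
- Five sessions against one consultation.

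**Assumed inputs, not in the article**

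- Phone share of 15 to 25% in the intervention arm and 5% in the control arm, an excess of 10 to 20 percentage points.
- Phone-minus-paper shift of 0 to 3 PHQ-9 points, in either direction.
- SD of 5 points.
- The minimum set collected by phone includes the PHQ-9.

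**Formula.** With the same shift in both arms, spurious arm difference = (phone share in intervention − phone share in control) × shift.

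**Yardsticks.** 0.30 × 5 = 1.5 points; 0.50 × 5 = 2.5 points.

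| Excess phone use | Size of shift | Arm difference | Of 1.5 points | Of 2.5 points |
|---|---|---|---|---|
| 0 | any | 0 | 0% | 0% |
| 10 points | 0 | 0 | 0% | 0% |
| 10 points | 1 | 0.10 × 1 = 0.1 | 7% | 4% |
| 10 points | 3 | 0.10 × 3 = 0.3 | 20% | 12% |
| 20 points | 1 | 0.20 × 1 = 0.2 | 13% | 8% |
| 20 points | 3 | 0.20 × 3 = 0.6 | 40% | 24% |

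**Cross-check by drop-out rate.** Let 50 to 100% of drop-outs be reached and the shift be 0.5 to 2 points, so that the difference is (excess drop-out) × (share reached) × (shift).

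- 10% v 10%: 0.
- 20% v 10%: 0.10 × 0.5 × 0.5 = 0.025 up to 0.10 × 1 × 2 = 0.2 points.
- 40% v 10%: 0.30 × 0.5 × 0.5 = 0.075 up to 0.30 × 1 × 2 = 0.6 points.

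**If the shift itself differs by arm.** A caller who knows the arm could produce different shifts in the two arms. The difference is then (share × shift) in the intervention arm minus (share × shift) in the control arm. With equal phone shares of 10% and shifts that differ by 1 point, it is 0.10 × 1 = 0.1 points. So the result is zero only if both drop-out and shift are equal (or if there is no shift at all).

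**The case against.** The strongest reply is that the rule is the same in both arms, so nothing in the article makes mode differ by arm. Drop-out is not defined. The sentence follows directly on the return envelopes, and a minimum set of outcomes makes most sense as a rescue when the full form has not come back. On that reading, session burden and travel do not matter: they hinder attendance, not posting a form. Control partners, who have had one talk and a booklet, might even return fewer forms. The article also asks partners and patients to complete questionnaires at every assessment, with no exception for those who stop sessions, so sending paper to everyone first may already be intended. Who calls, and with what script, is commonly left to the full protocol. Finally, phone retrieval limits missing data and serves the intent-to-treat aim.

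Much of this stands. A reader might infer that mode and assessor differ by arm, and that the intervention mean is pushed down to look like benefit. The documents do not support that. They give no arm-specific drop-out rate and do not say what the caller knows. Nor do they say that answers by phone are more favourable; people explaining why they left could equally report worse mood.

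What the objection does not remove is the rule as printed. Mode and collector change together for drop-outs, the reasons are sought in the same call, and no masking is stated in a trial declared unblinded. The other reading of drop-out, as leaving the programme, is just as natural beside the intent-to-treat sentence under Randomization procedure. Centres could therefore apply the rule differently.

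**Conclusion.** The point holds as a weakness in a stated collection rule, not as a demonstrated bias. Mode and collector of the self-report outcomes differ by drop-out status. They become related to arm if drop-out includes stopping sessions or is unequal for any other reason.

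Under the assumptions listed, the spurious difference lies between 0 and 0.6 PHQ-9 points in either direction, which is 0 to 40% of a 0.30 SD effect or 0 to 24% of the d = 0.50 behind the sample size. The upper end needs the largest excess phone use and the largest shift together. Zero is a possible value. Neither the sign nor the size can be derived from the article. The change is worth making because it is cheap and an unrecorded mode cannot be recovered afterwards.

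**What to change.** Reword the Follow-up assessments section to say the following:

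- Paper questionnaires go at t1 and t2 to every randomised partner and to that partner's patient, whether or not sessions were stopped.
- The phone is used only after non-return, by the same rule in both arms. This also settles what triggers the call.
- The caller reads the PHQ-9 and GAD-7 items verbatim and asks about reasons for drop-out only afterwards.
- Where feasible, the caller is an existing staff member who is not told the arm, for example from another centre.
- The mode of collection is recorded for each assessment.

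Keep phone scores in the main intent-to-treat analysis. Add a sensitivity analysis by mode, either adjusting for mode or treating phone scores as missing. Note in the plan that simply excluding them removes drop-outs selectively and can introduce attrition bias.

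The cost is a change of wording, one field on the form, one additional analysis and some coordination between staff or centres. Some participants may still reveal their arm during the call, so masking will be partial.
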